### Participants

#### Inclusion criteria

Only children meeting the following criteria are included:
All subjects must meet *DSM-5* criteria for Autism Spectrum Disorder. Diagnostic assessment is standardised according to *DSM-5* by performing the semi-structured Autism Diagnostic Interview (ADI-R), toddler algorithm with the parents, and the standardised Autism Diagnostic Observation Schedule-2 (ADOS-2) with the childAge range: 24–66 months old at T2Written informed consent of the legal caretakers of the patientAbility to regularly and reliably attend appointmentsParents ability and willingness to attend at least every fifth therapy session with the child

#### Exclusion criteria

Subjects presenting with any of the following criteria will not be included in the trial:
Non-verbal Developmental Quotient (DQ)/Intelligence Quotient (IQ) ≤ 30Non-verbal mental age ≤ 12 monthsDiagnosed vision or hearing impairments interfering with therapyCerebral palsyChronic neurological disorderUnstable epilepsyNeurodegenerative disorderRett/Angelman syndrome(History of) severe psychosocial deprivationInsufficient care by parentsAttachment disorderInstitutional upbringingParents not verbally fluent in German and/or unable to read German

#### Recruitment

The majority of the local ASD patients are diagnosed at the four participating study centres. Every ASD patient meeting the inclusion criteria will be invited to participate in the study. Additionally, flyers with information about the study will be provided at other medical and public facilities to reach more interested parents for inclusion. To promote participant retention and complete follow-up in all participants, the individual baseline and endpoint results of the ADOS-2 and the results of the developmental and cognitive tests will be provided and explained to the parents after the completion of the study. The families in the control group are offered participation in the A-FFIP intervention after completion of the study-related assessments after approximately 1 year. In case of any unexpected and unanticipated adverse events (AEs) of the intervention during the study (the assessment of serious adverse events (SAEs) is described under ‘Harms’), parents will be informed about these events prior to participation or during the study. Published research data will be shared with interested families by mail.

#### Withdrawal

Subjects may either withdraw from the intervention, but will stay in the study, or the subjects may totally withdraw from the study. A third option is that due to SAEs or other events, the principal investigator decides that the subject has to withdraw from the intervention. In all cases, the reason for withdrawal must be recorded in the patient’s Case Report Form (CRF) and in the subject’s medical records. In case of (full) withdrawal of a subject at the request of their legal representative, the reasons will be explored as extensively as possible. The subject will be followed up and – if possible – all examinations scheduled for the final trial day will be performed on all subjects and documented.

### Intervention to be investigated

The A-FFIP intervention manual [5] provides the clinical therapist (behaviourally trained psychiatrist/psychologist/social worker) with information on the theoretical background, description of the diagnostic assessments necessary before start of the intervention (including parent interviews), choice of individualised treatment targets, and a detailed description of the target-related specific exercises, including the toy-based training material (for more detailed information in English see attachment 1 of Kitzerow et al. 2019 [27]: https://econtent.hogrefe.com/doi/suppl/10.1024/1422-4917/a000661/suppl_file/1422-4917_a000661_esm1.pdf).

Intensive A-FIPP therapy training for all involved therapists will be done before treating children within the study. The therapy training comprises:
Individual study of the A-FFIP manualTwo participations in a 3-day workshop led by the first author of the A-FFIP manual and head of the Autism Intervention Centre at Frankfurt ([name]) *or* shadowing a qualified A-FFIP therapist of the Frankfurt group for 1 weekPractising the implementation of A-FFIP (planning of treatment targets, treatment principles, etc.) with a preschool-aged child with ASD not included in the study; video-documentation of intervention sessionsTargeted supervision based on these videos, which are rated prior to supervision by an experienced therapist based on the A-FFIP therapy fidelity checklistBased on the results of the therapy fidelity achieved by the therapist, the practising and supervision are repeated until a satisfying A-FFIP fidelity score is achieved:
*Total score* (range 0–56): 50 points*and**Item scores* (range 0–2): at least 1 point in each item

Continuous training and video-based telephone supervision will be provided by the Frankfurt group to ensure high treatment fidelity of therapists. The on-going supervision per centre comprises:
Every second session of the first five patients per centre and every eighth session of subsequent patients will be video recorded, sent to the Frankfurt supervision team and rated with the A-FFIP fidelity checklistDetailed feedback and supervision is provided by telephone once a month or in case of particular serious manual violations

An additional 2-day workshop once a year led by the first author of the A-FFIP manual with current questions by the therapists, examples from the supervisors and presentation of the current fidelity scores.

#### Setting

Sessions are provided in an outpatient setting at the respective study centre. All treatment rooms are furnished in a standardised way, with standardised and well-arranged play material, ensuring a structured environment providing orientation and a minimum of distraction.

The intervention comprises 2 h of intervention/week with two therapists working with the child. The two-therapist concept is an essential A-FFIP component. While the main therapist interacts with the child, the co-therapist acts as a shadow and prompts the child individually and in a situation-specific way, during the learning of new abilities, and only if necessary. This concept is believed to support the natural learning of the child, because the child will learn the specific skill or task faster, and the interaction with the main interaction partner (therapist/parent) is independent from any prompting efforts. If the child is very advanced and shows interest in social interaction with peers, two therapists will work with two equally advanced children. At least one parent is participating in a minimum of every fifth therapy session for psychoeducation and exercises with their individual child, with the aim of learning to use effective strategies for practising at home. Parents are asked to practise established skills at home in many naturally occurring situations; these tasks are determined by the therapist and the implementation is discussed regularly with the parents. To ensure compliance by supporting parents without increasing pressure, no specific amount of practising hours or situations is expected. Parental adherence and competence is assessed by a weekly questionnaire (PATCS, see section ‘Mediating mechanisms’).

If the child already attends kindergarten, one therapist visits the child’s kindergarten teachers, and (if existing) the personal assistant three times a year for individualised psychoeducation with the aim to support generalisation of the child’s acquired skills at kindergarten. The first appointment is organised directly at the beginning of the intervention.

#### Individualised treatment targets

The concept of A-FFIP is based on the individualised practising of developmentally based and highly specific treatment targets, taking latest research findings on ASD-specific development into account. This has been achieved by developing specific exercises based on developmental psychological science findings. Especially this third aspect is taking on, but also going beyond, current low-intensity NDBIs such as JASPER [13], PACT [14], pivotal response treatment [15] or imitation training [19], which focus on one or two core developmental aspects.

A-FFIP targets six core basic abilities (attentional control, joint attention, imitation, representation, planning, self/other distinction) and five developmental domains (language and communication, interaction and play, emotion regulation, cognition and adaptive behaviour).

For each of the core basic abilities and developmental domains, exercises for beginners, intermediate and advanced learners are provided in the A-FFIP manual. In addition, for each exercise, specific advice for therapists is given on how to correctly execute the exercises and how to teach parents the correct execution. The play material used is highly flexible according to the preferences of the child, increasing the child’s motivation to learn and to interact with the therapist. A-FFIP is an individualised intervention programme that takes the child’s current ability level into account [43, 45]. This rationale is essential due to the heterogeneous strengths and weaknesses of children with ASD in different developmental domains. A-FFIP expects the therapists to choose exercises that are slightly more advanced than the child’s current abilities promoting successful learning. Methods and exercises are highly standardised.

At the start of the A-FFIP intervention, a thorough assessment, based on ADOS-2 and Bayley Scales of Infant and Toddler Development – Third Edition (Bayley-III) results, play sessions with the child and parental report on the child’s behaviour at home, is done to elicit the abilities of the child in each of the basic and specific developmental domains. The collected information from the standardised instruments and from the direct observation is transferred to the detailed A-FFIP intervention targets checklist (for further information see attachment 1 of Kitzerow et al. 2019 [27]), which is the basis for planning the individual relevant interventions goals. Additionally, the parents are asked to complete a list of rewarding activities, and a broad range of positive rewards are tested at the beginning of therapy. Based on the results of this first assessment and parental priority, specific A-FFIP treatment targets are chosen together with the parents (maximum eight targets).

Progress in each area is monitored by the therapist filling in a specific documentation form adjusted to the A-FFIP intervention targets checklist after each session. Once the child has achieved a treatment target, a new target is focussed, which builds on the previous targets. Established skills will be trained in an ongoing fashion in different situations (e.g. at home with parents/siblings, at kindergarten) to assure generalisation.

#### Implementation of specific methods

A-FFIP has been developed on a strict empirical basis; therefore, effective, behaviourally based learning techniques are implemented, especially techniques supporting associative, operant, imitative and social learning (such as prompting, naturally based positive reinforcement, modelling, generalisation), and techniques reducing interfering, aggressive and stereotyped behaviour, such as antecedent- and consequence-based interventions [46] focussing on enhancing the child’s coping skills (e.g. by providing structure and routine). The child’s motivation to learn, play and socially interact is increased by natural reinforcement intrinsic to the child’s interests and activities, by therapist (and parental) synchrony, and by consistent positive reinforcement of self-initiated learning.

### Control intervention: early intervention as usual (EIAU)

For EIAU, individual or group therapy intensity of 1–10 h/week as well as waiting time prior to any intervention onset is allowed. This is representative for the German ASD preschool population, and comparable average intervention intensity per week is expected for both groups with higher variability for EIAU than A-FFIP [47].

### Additional treatments and medication use

In the A-FFIP as well as the EIAU groups, the following additional treatments are allowed: stable psychopharmacotherapy, stable medication for chronic medical conditions not interfering with the therapy, individual speech and language, occupational or physiotherapy, personal support at kindergarten/preschool or family support. Any additional treatment will be documented exactly (kind of intervention, dose, frequency, etc.) and will be compared for non-random distribution between groups in the statistical analysis.

Psychotropic medication will be started or changed at least 4 weeks before randomisation and will remain stable (mg/kg body weight) throughout the intervention (with the exception of dose adjustment to body-weight changes). The following psychotropic medication will be allowed as single or combined treatment: SSRI, other antidepressants, antipsychotic medication, atomoxetine, mood stabilisers. In addition, stable medication for the treatment of chronic conditions, such as allergies, asthma, epilepsy, enuresis, sleeping problems and intermitting medication for acute upper respiratory infections and diarrhoea, will be allowed. Pharmacological treatment will be documented at each time of assessment (T1-T6) and psychotropic medication effects on treatment outcome will be explored in analysing study outcomes.

Children in the Intervention group are permitted to receive any other intervention during the waiting time before the start of A-FFIP.

The following concomitant treatments are not permitted during the trial:
Additional general or ASD-specific early intervention (in the A-FFIP group)Additional parent training (in the A-FFIP group)Treatment in a day-care facility or ward of a child psychiatric department (A-FFIP and EIAU group)Elimination diets or therapy (A-FFIP and EIAU group)

Parents will be informed about these study requirements prior to inclusion and randomisation. If the clinical necessity arises to start any elimination diet or pharmacotherapy, this will be documented, and the child will be allowed to further participate in the study. If a child needs to be admitted for day-care or inpatient child psychiatric treatment, the child will have to stop participation in the study.

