#### Statistical methods

The primary analysis will be conducted based on the ITT population. Let *μ* denote the unknown true mean change of the BOSCC-AT between T2 and T6. The null hypotheses:

H_0_: *μ*_A-FFIP_ = *μ*_EIAU_ is tested against the alternative: H_1_: *μ*_A-FFIP_ ≠ *μ*_EIAU_.

The confirmatory test for treatment-group difference with respect to the primary efficacy endpoint will be done applying a mixed model for repeated measures (MMRM) approach [79] modelling the difference to baseline including the fixed-effects baseline BOSCC-AT, chronological age, treatment group, time, and treatment-group-by-time interaction; centre will be included as random effect. The time points of measurement are T2 (baseline), T4 (weeks 26–27) and T6 (weeks 52–54). The significance test for treatment-group difference will be based on least-squares means using a significant level of *α* = 5% (two-sided).

No missing data are expected for the covariates. Missing values for the primary outcome measure are dealt with as follows in the MMRM approach: The likelihood-based approach jointly models all actual observations without imputing missing data but using the within-patient correlation structure to provide information about the unobserved post-baseline primary outcomes and gives reliable results under the missing data at random (MAR) assumption. The MMRM approach shows favourable characteristics in terms of type-I error rate, power and bias of estimates as compared to alternative methods dealing with missing values, such as last-observation-carried-forward (LOCF) [79–81], even in the presence of a drop-out rate of 20% [82].

Data quality and homogeneity of intervention groups at baseline will be evaluated. All secondary endpoints will be analysed descriptively, using appropriate statistical methods.

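### The rule that psychiatric admission ends study participation conflicts with the Withdrawal section and can create avoidable missing T6 values in an ITT primary analysis (moderate)

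*Protocol article*

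**What the plan says.** All statements are in the protocol article.

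- **Additional treatments and medication use.** Treatment in a child psychiatric day-care facility or ward is not permitted in either arm. The consequence is: "If a child needs to be admitted for day-care or inpatient child psychiatric treatment, the child will have to stop participation in the study". The sentence before it deals with a child who has to start an elimination diet or medication: "this will be documented, and the child will be allowed to further participate in the study".
- **Withdrawal.** Two routes are open to families: "Subjects may either withdraw from the intervention, but will stay in the study, or the subjects may totally withdraw from the study". A third covers SAEs or other events, where "the principal investigator decides that the subject has to withdraw from the intervention". The section then asks for follow-up and, where possible, that "all examinations scheduled for the final trial day will be performed on all subjects and documented".
- **Statistical methods.** "The primary analysis will be conducted based on the ITT population". The model is an MMRM on change from baseline, with measurements at T2, T4 (weeks 26–27) and T6 (weeks 52–54). Missing outcomes are not imputed, and the method is said to be one that "gives reliable results under the missing data at random (MAR) assumption".
- **Additional analyses.** The sensitivity analyses named are per-protocol, LOCF and complete case.

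**The concern.** The Withdrawal section separates leaving the treatment from leaving the study, and a decision imposed by the principal investigator reaches only the treatment. The admission rule imposes an exit from the study itself. The word study does not look like a slip for intervention, for two reasons. The neighbouring sentence on diets and medication uses it to say that a child stays in. The rule also covers the control arm, whose treatment is delivered outside the study centres, so a control child has little to stop except the assessments.

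Admission happens after randomisation and may well accompany a worsening course. If assessments end there, the protocol itself produces missing primary-endpoint values. The primary analysis must then rely on MAR for those children, and none of the three named sensitivity analyses examines loss that depends on the unseen outcome. LOCF, for instance, would carry forward a value measured before the admission.

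**Working it through.** **1. The plan's own figure.** Inputs from Sample size calculation: effect size 0.55, two-sided α 5%, power 80%, 20% drop-out. The two-sample t test needs 52.87, so 53 per arm (power 0.801). Inflation gives 53 / 0.80 = 66.25, so 67 per arm and 134 in total. Both stated figures reproduce. The allowance of 67 − 53 = 14 children per arm protects the number analysed. It does not protect against bias if loss depends on outcome.

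**2. What is lost, by time of exit, if assessments stop at admission.**
- Before T4: no post-baseline value, so the child contributes nothing to a change-from-baseline model.
- Between T4 and T6: the T4 value stays in the MMRM, and T6 is inferred from values that precede the admission.

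**3. Bias formula.** For arm k, let q_k be the proportion whose T6 value is lost through admission, and g_k the amount, in SD of change, by which their unseen outcome is worse than MAR predicts. The model then overstates mean improvement in that arm by q_k × g_k, so

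bias in the A-FFIP advantage = q_A × g_A − q_E × g_E.

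With equal g this is (q_A − q_E) × g. If g = 0 in both arms, unequal admission gives no bias. If q and g are both equal between arms, the terms cancel.

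**4. Size under assumed inputs.** The article gives neither q nor g. Assumed: a difference in q of 3, 5 or 10 points (67 × 0.03 ≈ 2, 67 × 0.05 ≈ 3 and 67 × 0.10 ≈ 7 children) and g of 0.5 or 1 SD.

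| Difference in q | g = 0.5 | g = 1 |
|---|---|---|
| 3 points | 0.015 SD | 0.03 SD |
| 5 points | 0.025 SD | 0.05 SD |
| 10 points | 0.05 SD | 0.10 SD |

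As a share of the planned effect, the extremes are 0.015 / 0.55 = 2.7% and 0.10 / 0.55 = 18.2%. The standard error of the difference at 53 per arm is √(2/53) = 0.194 SD, so these biases are 0.08 and 0.52 standard errors. For 5 points and 1 SD it is 0.05 / 0.194 = 0.26.

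**5. Direction.** Take a true difference of 0.55 SD, and treat the lost outcomes as simply ignored, with g measured against the remaining children.
- Admissions 3% A-FFIP, 9% EIAU: the estimate becomes 0.52 (g = 0.5) or 0.49 (g = 1), with power at 53 per arm of 0.756 or 0.705.
- Admissions 2% and 10%: 0.51 or 0.47, power 0.739 or 0.669.
- Admissions 6% and 3%: 0.565 or 0.58, an overstatement.
- Admissions 3% and 3%, equal g: no shift.

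The MMRM would recover part of any such shift where T4 was observed.

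**The case against.** The strongest reply is that the sections can be read together. The Withdrawal section also allows total withdrawal, and its request for follow-up and final examinations comes after that, with no exemption for admitted children. The admission rule never mentions assessments. On this reading an admitted child stops participating but is still examined. This softens the conflict without removing it. The admission rule does not refer to the Withdrawal section, the request holds only where possible, and the final trial day could mean the day of exit. An examination at exit is not a week 52–54 measurement.

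A second reply is that admissions may be rare in children aged 24–66 months at baseline. A 10-point gap means about seven more admissions in one arm than in the other, and nothing in the article suggests that. This stands, and it limits the severity.

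A third is that analysis sets and intercurrent events belong in the analysis plan, which is not shown. That is right for the analysis, but no analysis plan can restore assessments that were never made.

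Three stronger readings are tempting, and the article does not support them:
- **That admitted children are removed from the ITT set.** The model uses every actual observation, so at most later visits are missing.
- **That unequal admission by itself biases the MMRM.** Step 3 shows that the unseen outcomes must also depart from the MAR prediction.
- **That admission is known to track BOSCC-AT change.** This is plausible, but it is stated nowhere.

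**Conclusion.** The concern holds as an inconsistency with a possible, unquantified effect on the primary endpoint. The admission rule, read as written, imposes an exit from the study. The Withdrawal section confines imposed withdrawal to the intervention and wants final examinations where possible, and the primary analysis is declared ITT. The resulting missing T6 values, and missing T4 values for earlier exits, would be avoidable.

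The range of 0.015 to 0.10 SD rests wholly on assumed admission differences and departures from MAR. Its upper end needs both extreme assumptions at once, so it should not be read as an estimate of what the trial will show. The sign depends on which arm has more admissions, so the rule cannot be called conservative. With few or balanced admissions the bias is close to zero. The sample size is unaffected. A reader might infer that the trial cannot proceed without this change, but with no admission rate given, moderate is the supportable rating.

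**What to change.** Reconcile Additional treatments and medication use, Withdrawal and Statistical methods on one question: does outcome assessment continue after admission? State that, whatever is decided clinically about treatment, an admitted child in either arm remains in follow-up for the scheduled T4 and T6 assessments unless consent is withdrawn. State also that all BOSCC data so collected enter the primary ITT analysis. Record the date of admission with the withdrawal reason, which the Withdrawal section already requires in the CRF. This concerns data collection only and takes no position on when a child should be admitted or treatment should stop.

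The cost is a protocol amendment. The ethics section requires written agreement of the parties, and an evaluation of whether formal approval and a revised consent document are needed. The visits are already scheduled and few in number, but may be harder to arrange for an admitted child. The numbers stay at 106 evaluable and 134 randomised. Including these children may move the estimated difference up or down, depending on which arm has more admissions.
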